### Power

We determined the power for the proposed main trial of this study. A total sample size of 530 (265 per group) will have 90% power at 5% significance (two-sided) to detect an absolute difference of 10% on the primary outcome between the 2 groups, assuming a control rate of 6.7% [19] and 20% loss to follow-up. Given the budget and resource limitations, in this study, we aim to recruit around (80/530, 15.1%) of the total sample size required for the main trial, that is, n=80 (40 per group), using an open recruitment strategy to recruit all participants within a month. At the end of the study, we will re-estimate the power of the final percentage differences between groups in the effectiveness report to further determine the exact final sample size of a full trial. The sample size is considered as a major limitation of the study.

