**Conclusions:**

If the SCAMPI program is shown to be preliminary effective, the study will be rolled out to be a future trial with a larger sample size and longer follow-up (6 months) to identify if it is an effective social network–based tool to support Chinese male smokers to quit smoking.

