## Methods

### Study Design

This study will be a pilot, two-arm, parallel RCT. We will evaluate the preliminary effectiveness and acceptability of our SCAMPI program as well as recruitment and retention for estimating the sample size of a future definitive trial. All trial procedures will be conducted web-based via WeChat (Tencent). Ethical approval was granted by the University of Auckland Human Participants Ethics Committee (reference number: 021649) and the Zhejiang University School of Public Health Research Ethics Committee (reference number: ZGL201801-2).

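### The full trial's exact size is to be set from the between-group difference seen in an 80-person pilot, which is too imprecise to size it and is measured at 6 weeks rather than 6 months

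*Protocol article*

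**What the plan says.** The Power section first gives a conventional calculation for the future trial: "A total sample size of 530 (265 per group) will have 90% power" at a two-sided 5% level, "to detect an absolute difference of 10% on the primary outcome between the 2 groups", with a control rate of 6.7% and "20% loss to follow-up". The pilot is fixed at 80 (40 per group) for budget reasons.

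The same paragraph then says what happens when the pilot ends: "we will re-estimate the power of the final percentage differences between groups in the effectiveness report to further determine the exact final sample size" of the full trial. It mentions no retained target difference, confidence limit or shrinkage.

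Three other places bear on this:
- Primary Outcome Measure: the pilot outcome is verified 30-day abstinence at 6 weeks.
- Abstract, Conclusions: if the program is shown to be preliminarily effective, a larger trial follows, with 6 months of follow-up.
- Study Design: among the pilot's purposes is to evaluate "recruitment and retention for estimating the sample size of a future definitive trial", listed after preliminary effectiveness and acceptability.

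**The concern.** A pilot with 40 per arm and a control rate near 7% expects about 3 quitters in the control arm and 7 in the intervention arm. A shift of one or two quitters changes the estimated difference greatly. Required sample size varies with the inverse square of that difference, so the error is magnified again. If the pilot is lucky, the full trial will be too small to detect the effect it was meant to detect. If it is unlucky, the full trial will look unaffordable even though the program works as assumed.

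The go-ahead depends on the pilot looking effective. That favours pilots whose observed difference is too large, and so favours undersized full trials.

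The difference being used is also a 6-week difference. Nothing in the article says how it would be carried to a trial with 6-month follow-up.

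**Working it through.** **Inputs.** From the Power section: two-sided 5%, 90% power, 6.7% control rate, 10-point difference (so 16.7%), 20% loss, 40 per arm in the pilot. From Retention: dropouts count as smoking, so the denominator stays at 40 per arm.

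**1. The plan's figure.** With unpooled variance:

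n = (1.96 + 1.2816)² × (0.067×0.933 + 0.167×0.833) / 0.10² = 211.85, so 212 per arm.

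212 / 0.8 = 265 per arm, total 530. This matches the stated size exactly, so this formula is used below. A pooled-variance formula gives 216 per arm, 270 after loss, total 540.

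**2. Precision of the pilot difference.**

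SE = √[(0.0625 + 0.1391)/40] = 0.071.

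95% half-width = 1.96 × 0.071 = 0.139. If the truth is 10 points, a typical interval is −3.9 to 23.9 points. The pilot's power for that difference is about 28%.

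**3. What the re-estimation would give.** For every pair of quitter counts (a of 40 control, b of 40 intervention), the observed rates a/40 and b/40 go into the formula of step 1. The result is weighted by its binomial probability at 6.7% and 16.7%. When b ≤ a there is no size.

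| Quantity | Result |
|---|---|
| 10th percentile of total N | 150 |
| 25th percentile | 244 |
| Median | 500 |
| 75th percentile | 1880 |
| No size exists (difference ≤ 0) | 10.6% of pilots |
| Total within a factor of 1.5 of 530 | about 24% of pilots |

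Single quitters drive the result: 3 against 7 gives 564, 3 against 6 gives 920, 3 against 5 gives 1880, and 2 against 8 gives 244. The pooled formula gives nearly the same quartiles (254, 508, 1888), so the finding does not depend on the choice of formula.

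**4. True power of the full trial so sized.** Take each computed N, analyse 80% of it, and evaluate power at the true 6.7% against 16.7%:
- Below 80%: 43.9% of all pilots. Among the 89.4% with a computable size, 0.439/0.894 = 49%.
- Below 50%: 15.9% of all pilots, and 0.159/0.894 = 18% of those with a computable size.
- Mean power where a size exists: 76%, against the intended 90%.

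The 24% and 18% depend on rounding. They round the evaluable number up before inflating for loss, as step 1 does. Rounding only once, at the end, gives 22% and 20%.

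**5. If the target stays fixed.** The reference size remains 530. Suppose the pilot updates only the loss rate and again finds 20%. With 80 people its 95% half-width is 1.96 × √(0.2×0.8/80) = 8.8 points, so roughly 11% to 29%. The total then moves only between about 478 and 596.

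**The case against.** **The sentence need not mean a mechanical plug-in.** It gives no formula, and it does not say that 530 or the 10-point target is dropped; it could mean refining 530 with judgement. This stands as a limit on the figures, which describe the plug-in reading. No reading, however, separates the exact final size from the observed percentage differences, and no floor or interval is stated.

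**Nothing in the pilot depends on it.** This stands. The pilot's size, randomisation, outcome and comparison are untouched, and a later trial would need its own justification. It limits the severity.

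**The median re-estimate is close to 530.** True: 500. A reader might therefore call the resulting size close to random, and that says too much. The rule is roughly centred; the fault is its spread.

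**Pilots with no computable size would simply not proceed.** Fair, since rollout is conditional on preliminary effectiveness. The power figures in the verdict are therefore restricted to pilots where a size exists.

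**The authors acknowledge the small sample.** They do, as a major limitation in the Power section and again in the Discussion. That acknowledgement does not fit with taking an exact size from the same sample.

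Two stronger readings are tempting and are not supported:
- A reader might infer that Study Design contradicts Power, because it names recruitment and retention as the sizing inputs. The same sentence lists preliminary effectiveness first, and the sizing purpose can govern the whole list. The passages are compatible.
- A reader might infer that the full trial is tied to the wrong endpoint. The article never defines the full trial's primary endpoint; it gives only a 6-month follow-up. What can be said is that a 6-week difference does not by itself estimate a 6-month one, and that no bridge is given. How far the effect would persist is not in the document, so no figure is put on it here.

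**Conclusion.** The point holds as a fault in a stated rule and should be fixed, but it does not threaten the pilot. Sizing the definitive trial is a declared purpose of this study, and the stated way of doing so serves that purpose badly. Even if the program performs exactly as assumed, half of the re-estimated sizes lie outside 244 to 1880. Where a size can be computed, the full trial falls below 80% true power about half the time (49%), with a mean of 76%. The condition that the pilot look effective pushes the trials that go ahead towards the undersized end.

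These figures assume that the observed rates are entered directly into the plan's own formula with 20% loss, that 6.7% and 16.7% are the true rates, and that the 10-point effect holds unchanged at the full trial's endpoint. The figure of 530 itself is correct.

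**What to change.** Replace the re-estimation sentence in the Power section with text to this effect:
- The full trial remains sized on the prespecified 10-point difference, with 530 as the reference, once the team has confirmed that 10 points is the right target at the full trial's own endpoint. The article does not call it a minimum worthwhile effect, so this needs an explicit decision.
- The observed pilot difference, and any power computed from it, will not set the size. It will be reported with its 95% confidence interval.
- The pilot updates recruitment and loss to follow-up.
- The pilot control rate is used only as a sensitivity range, with its interval and a note that it is a 6-week rate. It too comes from 40 men: at 6.7% its half-width is 1.96 × √(0.0625/40) = 7.7 points.

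Totals with the 10-point difference, 90% power and 20% loss held fixed:

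| Control rate | Total N |
|---|---|
| 5% | 460 |
| 6.7% | 530 |
| 10% | 658 |
| 15% | 828 |
| 20% | 974 |

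(The last row is 972 if rounding is done only once.)

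The cost is one reworded paragraph and this table. The one loss is that the pilot no longer delivers a single exact sample size.

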### Ethics Approvals

Ethics approval (reference number: 021649) was obtained from the University of Auckland Human Participants Ethics Committee. As this study targets Chinese male smokers, ethics approval (reference number: ZGL201801-2) was obtained from the Zhejiang University School of Public Health Research Ethics Committee.

### Consent

All eligible individuals are given an electronic copy of the information sheet and informed consent form to read via WeChat. The information sheet provides a summary of the study, and the informed consent document states what the individual is about to participate in, the individual’s rights as a research participant, and information about confidentiality. Individuals are encouraged to communicate with researchers through SCAMPI OA if they need any further explanation or information about the study. If the person chooses to participate in the study, that person will be asked to tap the *agree* button on the informed consent page of the registration questionnaire (Multimedia Appendix 5). Subjects who refuse to participate or who withdraw from the study were treated without prejudice. The reason for refusal or withdrawal will be noted if reported.

### Confidentiality

All study-related data will be exported and stored securely at the university server under a coded identification number to maintain participant confidentiality. All data that contain personal identifiers, such as screening data for eligibility and informed consent forms, will be stored separately from study records identified by a code number. All local databases were secured with a password-protected access system. All data of the study were collected and stored electronically.

## Discussion

### Principal Findings

This pilot trial and its findings will contribute to the evidence available to inform the development and implementation of the SCAMPI program as a mobile social network–based smoking cessation tool. The primary outcome of the study was to contribute to an understanding of the preliminary effectiveness of the SCAMPI program as a smoking cessation intervention for the target population. The overall implementation of the study can have an impact on delivering smoking cessation interventions through social network platforms such as WeChat. The use of the SCAMPI program is not restricted to any specific place, time, or situation, and it is free to use. It can also contribute to the reduction of health care costs. In addition, the study will contribute significantly to future research on social network–based health intervention development and evaluation. It may provide new ideas about applying social network platforms to improve recruitment efficiency and engagement in public health research projects. The relatively small sample size and short-term follow-up due to time and budget limitations are common with mobile smoking cessation trials [40], which is a threat to the quality of the trial.

### Trial Status

Recruitment for this project commenced in January 2019 and was completed in the same month. Follow-up data collection commenced and was completed by the end of June 2019.

## Appendix

Multimedia Appendix 1 Development Questionnaire.

Multimedia Appendix 2 Usability Testing Questionnaire.

Multimedia Appendix 3 Transition from behavioral factors to behavior change techniques.

Multimedia Appendix 4 Screenshots and Quick Response codes of the program.

Multimedia Appendix 5 Registration Questionnaire.

Multimedia Appendix 6 End-of-trial Questionnaire.

## Abbreviations

BCT: behavior change techniques
BCW: behavior change wheel
CCSCG: China Clinical Smoking Cessation Guideline
COM-B: capability, opportunity, and motivation to behavior
CPD: collaborative product development
MARS: Mobile App Rating Scale
OA: official account
QR: Quick Response
RCT: randomized controlled trial
UCD: user-centered design
UI: user interface
UX: user experience
